# **Study Protocol**

## **Acceptability and Efficacy of an Innovative Soya Maize Based RUTF for the Treatment of Severe Acute Malnutrition**

**29 October 2014**

**Valid Nutrition for a partnership study with Ajinomoto**

# 1 Executive summary

## 1.1 Background:

Ready to Use Therapeutic Foods (RUTF) have been used widely in Community based Management of Acute Malnutrition programmes (CMAM) to treat severe acute malnutrition (SAM) in children in resource-poor settings. Hitherto, most of the RUTF used in CMAM programmes uses cow milk as the main protein source. The use of cow milk at 25% by weight of the final product in these formulations makes them too expensive for sustainable use in resource-poor settings. At the same time attempt to produce free or low milk content RUTFs has yielded contrasting results with the most promising formulation being as effective as the standard formulation only in children aged 24 months or more. Thus, innovative free or low cow milk alternatives are needed.

Only two studies both conducted by Valid, have tested alternative milk-free recipes that are based on locally produced cereals and legumes for efficacy among SAM children. These studies have revealed that this milk-free RUTF is as effective as the standard RUTF in children two years and more but less effective than the standard RUTF in children less than two years at the beginning of treatment. Possible explanations for this include sub-optimal levels of key amino acids (AA) involved in protein synthesis during this period of rapid growth. Studies have recently demonstrated that SAM children have high requirements of certain AA and that supplementation with these AA at the initiation of the treatment or during the phase of catch up growth may improve protein synthesis and support faster recovery.

One of Valid's studies included a component of body composition assessment using the deuterium dilution technique in one sub-sample and using bio-electrical impedance in another sub-sample. The deuterium revealed that none of RUTF was associated with excess fat deposition. Both sub-studies revealed that they may be a subtle difference between the two RUTFs that could partially explain the quality of synthesised tissues. From the results it could be hypothesised that catch up in linear growth may happen at the expense of repair of cellular membranes. These findings need to be confirmed in a study with a bigger sample size and subsequently the AA profile of the new SMS-RUTF should be improved to be near equivalent to that of the reference protein.

The international nutrition community are now pushing for an integration of programs that address stunting with programs that address acute malnutrition. Data have shown that most children with severe acute malnutrition are also stunted. Having a product that will reverse wasting while also promoting catch up in linear growth is needed. Such a product will support feasibility and success of the process of integration.

## 1.2 Goal:

The goal of this research programme is to assess in two different phases the acceptability (phase 1) and the efficacy (phase 2) of two innovative Soya-Maize-Sorghum RUTFs for the treatment of SAM in children under five years old. The two products are the new version of the Milk Free Soya-Maize RUTF (FSMS-RUTF) and the 10% Milk Soya-Maize-Sorghum RUTF (MSMS-RUTF). The new SMS-RUTF has an improved AA profile compared to the previous milk free SMS-RUTF and less phytic acid.

## **Phase 1: acceptability**

### **Primary hypotheses:**

- 1 FSMS-RUTF and MSMS-RUTF have organoleptic characteristics (taste, smell, texture, colour) as acceptable as the standard milk and peanut based RUTF (P-RUTF) for Malawian children aged 3 to 5 years attending community based child care centres (CBCC)
- 2 FSMS-RUTF or MSMS-RUTF intake will not be associated with more RUTF related side effects than P-RUTF in Malawian children aged 3 to 5 years attending CBCC.

### **Secondary hypothesis:**

- 3 FSMS-RUTF and MSMS-RUTF will not be associated with a higher level of breath hydrogen excretion when compared to P-RUTF.

## **Phase 2: efficacy**

### **Primary hypotheses:**

- 1 Recovery rate of children aged 6 to 23 months with SAM treated with FSMS-RUTF is  $> 75\%$  and is not inferior to that of children with SAM of the same age treated with MSMS-RUTF nor to that of P-RUTF with the fixed non-inferiority margin being 10%.
- 2 Recovery rate of children aged 24 to 59 months with SAM treated with FSMS-RUTF is  $> 75\%$  and is not inferior to that of children with SAM of the same age treated with MSMS-RUTF nor to that of P-RUTF with the fixed non-inferiority margin being 10%.

### **Principal secondary hypotheses:**

- 1 Weight gain (g/kg/day) during of children aged 6 to 59 months with SAM treated with FSMS-RUTF is not inferior to that of children with SAM of same age treated with MSMS-RUTF nor to that of those treated with P-RUTF with the fixed non-inferiority margin being 1.5g/kg/day (age group 6 to 23 months and 24 to 59 months to be sampled and analysed separately).
- 2 Time to recovery under treatment from admission to recovery of children aged 6 to 59 months with SAM treated with FSMS-RUTF is within the non-inferiority margin of 14 days when compared to children of the same age treated with MSMS-RUTF or to P-RUTF (age group 6 to 23 months and 24 to 59 months to be sampled and analysed separately).
- 3 Height gain during recovery and 3 months after discharge of children aged 6 to 59 months (admission age) with SAM treated with FSMS-RUTF is not inferior to that of children with SAM of the same age treated with MSMS-RUTF nor to that of children treated with P-RUTF given a fixed non-inferiority margin of 0.5 cm (age group 6 to 23 months and 24 to 59 months to be sampled and analysed separately).
- 4 Proportionally to body weight, percentage of body fat mass (BFM) measured at the time of recovery of children treated with FSMS-RUTF will not be higher than the percentage of BFM in children treated with MSMS-RUTF nor higher than the percentage of BFM of those treated with P-RUTF at the fixed margin of inferiority of 6%.
- 5 Tissues electrical properties assessed by Bio-electrical impedance analysis (BIA) will not be impaired in children treated with FSMS-RUTF when compared to that of children treated with MSMS-RUTF or with P-RUTF given a margin of equivalence to be determined by the synthesis methods based on findings of the SMS-RUTF study recently completed in DRC.

### **Other secondary hypotheses:**

- 6 Haemoglobin gain of children treated for SAM with FSMS-RUTF will not be lower than that of children treated with MSMS-RUTF nor than that of those treated with P-RUTF given a margin of non-inferiority of 0.5g/dl.
- 7 The RUTF daily intake in grams and in kcal/kg/day of children 6 to 59 months old treated for SAM with FSMS-RUTF will not be inferior to the daily intake of children of the same age treated with MSMS-RUTF nor to the daily intake of those treated with P-RUTF given a margin of non-inferiority of 18g/day and 25kcal/kg/day (age group 6 to 23 months and 24 to 59 months to be sampled and analysed separately)
- 8 Breast milk intake of children 6 to 23 months old treated for SAM with FSMS-RUTF will not be lower than the breast milk intake of children of the same age treated with MSMS-RUTF nor to the intake of those treated with P-RUTF given a margin of non-inferiority of 100g/day.
- 9 Proportion of children with normalised stool calprotectin at 14 days, 28 days and recovery will not be lower in children treated for SAM with FSMS-RUTF than in those treated with MSMS-RUTF or in those treated with P-RUTF given a margin of non-inferiority determined using the synthesis method based on the confidence interval observed in children treated with P-RUTF.
- 10 Plasmatic level of key growth related AA of children treated with FSMS-RUTF will not be inferior to that of children treated with MSMS-RUTF or P-RUTF given a margin of non-inferiority defined using the synthesis method
- 11 12-months after discharge survival in children with SAM treated with FSMS-RUTF will not be inferior to that of children treated with MSMS-RUTF nor to that of those treated with P-RUTF given a margin of non-inferiority of 10%.

### **1.3 Rationale:**

P-RUTF has been shown to be efficacious in the treatment of SAM in children but it contains 25% cow milk-powder that is often exclusively imported. This makes local production in affected developing countries complex and costly. The use of alternative foodstuffs that are locally grown may offer an affordable option. Further, the utilisation of locally grown foodstuffs for RUTF production may provide ready markets for agricultural produce, and in this way, increase the income of local people. Available data confirm that milk-free RUTF can be used as alternative to the standard P-RUTF in children 24 months or older but that there is need of optimisation of the formulation for those below 24 months of age. The present study will test a modified formulation of SMS-RUTF. The modification in the formulation consists of improving the amino acid profile using an amino acid mixture (FSMS-RUTF) or including cow milk at 10% weight of the final product. It is expected that these changes will improve recovery rate in children of all ages.

### **1.4 Potential impact on child health:**

There is good evidence of the benefit of RUTF in reducing case-fatalities among children suffering from SAM. Its use in CMAM programming has been shown to reduce SAM related mortality from 20-30% to below 5% while increasing programme coverage from below 10% to around 50%. It has also been shown that health benefits may extend to achieving better long term survival than the general population of the same age and same community. Emerging evidence suggest that there may be relationship between severe acute malnutrition and stunting. It is likely that improving the coverage of SAM treatment may also contribute to the reduction of the burden of stunting.

### **1.5 Methods:**

#### **1.5.1 Design:**

The acceptability trial will be a cross-over study with the two RUTFs to be tested compared individually with the standard RUTF. At this stage there will not be comparison between FSMS-RUTF and MSMS-RUTF. The

efficacy trial will be a three arms statistician blinded, randomized and controlled, parallel group, efficacy non-inferiority trial. The two study foods will be compared individually with the standard RUTF and there will also be a comparison between the two study foods.

## **1.5.2 Methodological approaches and procedures:**

### **1.5.2.1 Acceptability trial**

Children aged 3 to 5 years with MUAC below 12.5 cm regularly attending the selected community based child care centres (CBCC) will be eligible for the acceptability trial. Children will be divided in 4 groups. In 2 separate phases, each group will alternatively receive one of the study food (FSMS-RUTF or MSMS-RUTF) and the control food (P-RUTF). Two CBCC will be used with each site testing a separate study food. Three meals per day of either the study food or the control food will be served 5 days per week during 2 consecutive weeks at the dose of 92g/day. The 2 phases will be separated by two weeks (washout time).

MUAC, weight and height measurements, body temperature, respiratory rate, a clinical assessment when required, hydrogen breath test, observation of general response to food administered and a caregiver's interview will be the only procedures carried out during the acceptability trial. Data will be collected daily, on pre-defined data collection form. Hired research enumerators will collect the data with the help of CBCC workers.

### **1.5.2.2 Efficacy trial**

Children staying within 1 hour walking distance from feeding points especially established in the community for the study will be enrolled and will be followed up from admission to nutrition recovery using a day care approach. Enrolled children will attend the site daily from 9 am to 3 pm. Children will be offered 200kcal/kg/day of one of the study RUTF. Children will be declared non-recovered if they don't meet the discharge criteria ( $MUAC \geq 12.5$  cm and no oedema) after 3 consecutive months of treatment. Apart from the difference in study therapeutic food, children of all the three study groups will be treated in the same way in accordance with the national guidelines for the treatment of SAM but using the day-care approach as stated above. The day-care approach allows the elimination of several confounding factors such as sharing or poor intake of the therapeutic food at households' level, inappropriate intake of routine medicines and differences in the product acceptance by caregivers that may affect child feeding of the study food. This approach will also allow close monitoring of side effects such as abdominal pain due to iron intake, flatulence (due to unabsorbed sugar), diarrhoea due to lactose intolerance and appetite suppression due to some oligosaccharides. Anthropometric parameters will be measured daily (weight and MUAC) or weekly (height). Clinical conditions will be assessed daily (appetite, oedema, cough, difficulty of breathing, diarrhoea, dehydration, fever, skin eruption, neurological status, anaemia). Embedded sub-studies will allow the assessment of

- haemoglobin (admission and discharge) with an Haemocue device that uses capillary blood collected at finger prick;
- body composition using deuterium dilution technique (at discharge for both those who recovered and those who did not recover);
- body composition using bio-electrical impedance analysis (at admission or when oedema subside, at time of reaching discharge criteria, at discharge and at 3 months follow up) using a Bodystat 1500 MDD device;
- breast milk intake using the dose-to-mother deuterium oxide dilution technique in children still breastfed at admission (two weeks after the start of the treatment);
- stool calprotectin using a quantitative point-of-care chromatographic immunoassay kit for the assessment of intestinal inflammation (admission, 28 days after the start of treatment, at discharge)
- free serum amino acid profile using venous blood.
- Post-discharge mortality will be assessed 12 months after nutrition recovery.

All data will be collected on a modified version of the standard clinic cards used for monitoring treatment of SAM. Data of some specific procedures including body composition assessment, breast milk intake assessment and amino acid profile assessment will be collected on separate forms specially designed for the sub-studies.

### **1.5.3 Sample size:**

#### **1.5.3.1 Acceptability trial**

We will use a convenience sample of 20 children per group (40 children per study site) equivalent to 40 children testing one study food in a cross-over design and a total of 80 children used for the acceptability trial (2 sites). At each site 20 children will start with a study food (FSMS-RUTF or MSMS-RUTF) and shift to P-RUTF during phase 2 of acceptability. Twenty other will start with P-RUTF and shift to the study food during phase 2 of acceptability.

#### **1.5.3.2 Efficacy trial**

The sample size is calculated based on the primary objectives only. A minimum of 750 SAM children below 24 months of age and 450 SAM children 24 to 59 months of age is required to be 80% sure that the upper limit of a one-sided 95% confidence interval will exclude a difference in recovery rate in favour of the standard group of more than 10%. In addition 60 community control children will be enrolled for the Deuterium dilution technique sub-study. The number of children to be enrolled as community control of children discharged alive and for whom the follow up is possible will depend on the number of children meeting follow up eligibility criteria.

### **1.5.4 Analysis:**

#### **1.5.4.1 Acceptability trial**

The acceptability and the tolerance will be judged based on the criteria listed below

- Persistence of good appetite
- Consumption of more than 75% of the offered food within 1 hour. (meal acceptance)
- Consumption of more than 75% of the offered food for more than 75% of the days on trial (overall acceptance)
- Frequency of ill-effects associated with the food requiring withdrawal from the trial is less than 10%.
- Consumption of a quantity of energy not less than 75% of the energy intake from the control food.

The organoleptic characteristics (taste, colour, smell, texture) will be assessed using a 5-points likert scale validated for the age group 3 to 5 years. Data will be analysed by comparing the mean scores of the study foods (FSMS-RUTF or MSMS-RUTF) for each organoleptic characteristic with the score of the control food which is the P-RUTF.

#### **1.5.4.2 Efficacy trial**

Appropriate quantitative analysis will be used including descriptive statistics (proportion, percentage, mean or median), comparison of difference in proportion for binary outcome and comparison of average (mean or median as appropriate) change for continuous variable. Both intention to treat (ITT) and per protocol (PP) approaches will be used for data analysis and reporting. Data of children below 24 months and that of those aged 24 months or more will be analysed separately except for body composition and haemoglobin. Subgroup analyses assessing the effect of the intervention in different subgroups will be carried out. The variables considered for the sub-group analyses include gender, type of malnutrition (oedematous and non-oedematous) stunting and HIV status (positive or negative). Interactions between the interventions and other variables will be checked and data analysis scheme adjusted accordingly in case of a statistically significant interaction. No interim analysis will be performed except if the monitoring and safety committee identify need for such analysis.

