## 2.5.3 Sample size and randomisation

### 2.5.3.1 Sample size

For the acceptability trial, a convenience sample of 20 children per group will be used. For assessing efficacy, the different sample sizes are calculated for a power of 80% and a level of significance of 0.05. The total sample size will be the total of sample required for the SO1 and SO2. For the other SOs, the calculated sample was lower than that required for the total sample for SO1 and SO2 as indicated in table 2 below.

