| SO7                | Mean
Fat free mass (%)                          | Non-inferiority
clinical trial | Standard deviation=1.62
Margin of non-inferiority = 1.07kg
Loss to follow up=5%                            | 35 per arm
Total=105 children
6-59 months |
| SO8                | Mean
Phase Angle                                | Non-inferiority
clinical trial | Standard deviation=0.7
Margin of non-inferiority = 0.2
Loss to follow up=10%                               | 170/arm
Total= 510 children
6-59 months   |
| SO9                | Mean
height gain
3 months after
discharge | Non-inferiority
clinical trial | Standard deviation=0.7
Margin of non-inferiority = 0.5cm
Loss to follow up=10%                             | 180 /arm
Total=540 children
6-23 months   |
| SO10               | Mean
height gain
3 months after
discharge | Non-inferiority
clinical trial | Standard deviation=0.8
Margin of non-inferiority = 0.3 cm
Loss to follow up=10%                            | 100 /arm
Total=300 children
24-59 months  |
| SO11               | Anaemia rate                                       | Non-inferiority                   | Standard deviation=1.3
Non-inferiority margin = 0.5 g/dl
Loss to follow up=10%                             | 100 /arm Total=300
children (both age group) |

The sample size for non-inferiority assessment is calculated using the software “Power” available at [http://www.sealedenvelope.com/power\\_binary\\_noninferior.php](http://www.sealedenvelope.com/power_binary_noninferior.php) for binary endpoint and [http://www.sealedenvelope.com/power\\_continuous\\_noninferior.php](http://www.sealedenvelope.com/power_continuous_noninferior.php) for continuous endpoint. For binary endpoint, the software uses the formula  $n = f(\alpha, \beta) \times [\pi_s \times (100 - \pi_s) + \pi_e \times (100 - \pi_e)] / (\pi_s - \pi_e - d)^2$  where  $\pi_s$  and  $\pi_e$  are the true percent 'success' in the standard and new (experimental) treatment group respectively  $f(\alpha, \beta) = [\Phi^{-1}(\alpha) + \Phi^{-1}(\beta)]^2$  and  $\Phi^{-1}$  is the cumulative distribution function of a standardised normal deviate [94]. For the continuous endpoint, the Calculation is based on the formula:  $n = f(\alpha, \beta) \times 2 \times \sigma^2 / d^2$  where  $\sigma$  is the standard deviation and  $f(\alpha, \beta) = [\Phi^{-1}(\alpha) + \Phi^{-1}(\beta)]^2$  [95].

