### **2.5.3.2 Randomisation**

The study will use simple randomisation and the sealed opaque envelope method will be used for the final allocation of group.

For the acceptability trial, using a pre-established list of sites, eligible children with their caregivers will be invited one by one and asked to pick an envelope containing the study group from a sealed box. No change of envelope will be allowed.

For the efficacy trial, to minimize selection bias and maximize chances of having balanced allocation in all the 3 study groups, a block randomisation with random block size scheme will be used. Thus, in blocks of different sizes (the size will be decided in advance and randomly), children will be prospectively allocated to one of the 2 intervention groups (FSMS-RUTF group or MSMS-RUTF group) or the control group in which the standard RUTF (P-RUTF) will be used. Different randomisation list will be established for 6 to 23 months and 24 to 59 months children.

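### Pooled body composition, phase angle and haemoglobin comparisons do not name the randomisation age group as a factor: a free precision gain on secondary endpoints, not a bias

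*Protocol*

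**What the plan says.** Section 2.5.3.2 (Randomisation) states for the efficacy trial that "a block randomisation with random block size scheme will be used" and that "Different randomisation list will be established for 6 to 23 months and 24 to 59 months children". Age group is the only stratification factor named.

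Section 1.5.4.2 (Analysis, efficacy trial) says that the two age groups "will be analysed separately except for body composition and haemoglobin". For continuous variables it describes a comparison of mean or median change. Its subgroup variables are gender, oedematous or non-oedematous malnutrition, stunting and HIV status. Section 2.5.6.2.1 lists gender, form of SAM and HIV status for the interaction checks. Age group is in neither list. The only place where age is named as a model term is the post-discharge survival model, as age at discharge.

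Table 2 agrees with the pooling. Fat free mass (SO7) and phase angle (SO8) are sized for children of 6 to 59 months, and haemoglobin (SO11) for both age groups together. Phase angle counts here as body composition because section 1.5.2.2 describes bio-electrical impedance as a body composition measurement.

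**The concern.** When a trial is randomised within strata, the natural analysis carries those strata. Here the age split is removed for three sets of outcomes and the text names nothing in its place. Age is also the factor that the protocol treats as most important: sections 1.1 and 2.1 report that the earlier milk-free food matched the standard from 24 months upwards but did worse below that age.

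If these outcomes differ between the age groups, an unadjusted pooled comparison leaves that difference in the error term. Two consequences are possible, under different conditions:

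- **Balanced age mix across arms.** The usual standard error is larger than the true one, so the intervals are wider than necessary.
- **Age mix left to chance in a sub-sample.** The protocol states no age quota for the sub-studies. Arms may then differ in age, which moves the estimate in any one sample. The ordinary standard error allows for this, but adjustment would remove it.

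What is at stake is precision on secondary endpoints.

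**Working it through.** **Inputs.** Section 2.5.3.1 gives "a power of 80% and a level of significance of 0.05", and section 1.5.3.2 refers to "the upper limit of a one-sided 95% confidence interval", so alpha is taken as one-sided 0.05 (z = 1.645, with 0.842 for power). From Table 2:

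- Phase angle: "Standard deviation=0.7", margin 0.2, 10% loss, 170 per arm.
- Fat free mass: "Standard deviation=1.62", "Margin of non-inferiority = 1.07kg", 5% loss, 35 per arm.
- Haemoglobin: SD 1.3, margin 0.5 g/dl, 10% loss, 100 per arm.
- Age mix: 250 younger and 150 older children per arm, so w = 250/400 = 0.625.

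**Step 1: the stated sizes.** n = 2 × SD² × (1.645 + 0.842)² / margin², then divided by (1 − loss).

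- Phase angle: 2 × 0.49 × 6.18 / 0.04 gives 152, then 169. Stated: 170.
- Haemoglobin: 2 × 1.69 × 6.18 / 0.25 gives 84, then 94. Stated: 100.
- Fat free mass: 2 × 2.6244 × 6.18 / 1.1449 gives 29, then 31. Stated: 35.

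Phase angle reproduces. The other two exceed the formula, so none is short on this basis.

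**Step 2: variance added by pooling.** With D the difference between age-group means in within-group SDs, the pooled variance is V = 1 + w(1 − w)D² times the within-group variance, and w(1 − w) = 0.625 × 0.375 = 0.234. D is not in the documents, so the range 0 to 1 is an assumption.

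| D | V | SE ratio √V |
|---|---|---|
| 0 | 1.000 | 1.00 |
| 0.5 | 1.059 | 1.03 |
| 1.0 | 1.234 | 1.11 |

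**Step 3: phase-angle power with adjustment.** Evaluable children per arm: 170 × 0.9 = 153. Reading 0.7 as the total SD, the adjusted SD is 0.7/√V and power is Φ(0.2/SE − 1.645), with SE = (0.7/√V) × √(2/153).

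| D | SE | 0.2/SE | Power |
|---|---|---|---|
| 0 | 0.0800 | 2.50 | 80.3% |
| 0.5 | 0.0778 | 2.57 | 82.3% |
| 1.0 | 0.0720 | 2.78 | 87.1% |

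On the same reading, the sizes needed with adjustment (including loss, for D = 0, 0.5 and 1) are 169, 160 and 137 for phase angle, 94, 88 and 76 for haemoglobin, and 31, 29 and 25 for fat free mass. All are within the stated sizes.

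If instead 0.7 is the within-group SD and the age mix is balanced, unadjusted power is Φ(0.2/0.0800 − 1.645√V): 80.3%, 79.0% and 74.9%. Adjustment keeps it at 80.3%.

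**Step 4: error rate without adjustment, balanced age mix.** The nominal one-sided 5% becomes 1 − Φ(1.645√V): 5.0%, 4.5% and 3.4% for D = 0, 0.5 and 1. That is conservative.

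**Step 5: chance imbalance in the smallest sub-sample.** Evaluable children per arm: 35 × 0.95 ≈ 33. If they are drawn without regard to age, the SD of the between-arm difference in age mix is √(2 × 0.234/33) = 0.119, about 12 percentage points. At D = 1, a 12-point imbalance moves the arm difference by about 0.12 within-group SD, and at D = 0.5 by about 0.06. No kilogram figure is offered, because Table 2 labels SO7 as a percentage but states its margin in kg.

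**The case against.** The best counter-argument is that pooling over strata is not the same as leaving the stratum out. The protocol gives no full model for these endpoints, its list of methods is open-ended, and it says that the analysis will be adapted if interactions are found. Covariates are commonly fixed in a statistical analysis plan, and none is among the documents. This stands in part: the protocol does not forbid adjustment. But it describes a comparison of averages and names several variables of interest without age group, so adjustment is not secured as written.

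Other objections stand fully:

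- Several of these outcomes are changes within a child (haemoglobin gain, change in phase angle). Change removes stable differences in level, so D may be small, and at zero nothing is gained.
- Read with a total SD of 0.7, unadjusted phase-angle power already meets the planned 80%.
- The two consequences do not apply together. A balanced mix gives conservative intervals, and an unbalanced one gives noise that the ordinary standard error already covers.

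A reader might infer that the pooled comparisons are confounded by age. The documents do not support that: the planned 250 and 150 per arm give every arm the same mix, and chance imbalance in a sub-sample is not bias in expectation. Nor is the pooling a contradiction. The objectives for body composition, phase angle and anaemia carry no separate-analysis clause, and Table 2 sizes them on both age groups.

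**Conclusion.** The point holds as an optional improvement in precision on secondary endpoints. The only stratification factor is not named in the only between-arm comparisons expressly pooled over it. For an assumed gap of 0, 0.5 or 1.0 within-group SD, this leaves 0%, 6% or 23% extra variance. With adjustment, phase-angle power would be 80%, 82% or 87%.

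These figures rest on a 62.5:37.5 age mix in the sub-samples, one-sided alpha of 0.05, 0.7 read as the total SD, and a gap that the documents do not give. A reader might take the omission as an error that invalidates a result or leaves a sample size short. Neither follows: type I error is not inflated, and every stated size covers its own calculation at one-sided 0.05.

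**What to change.** In section 1.5.4.2, after the sentence on separate analysis by age, add: *Pooled analyses of body composition, phase angle and haemoglobin include the randomisation age group (6-23, 24-59 months) as a factor.*

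The cost is one sentence. Age group is known for every child at randomisation, so no new data are needed. No stated sample size changes, and the pooling stays as planned.
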